## Abstract

**Background:**

The standard treatment pathway for locally advanced rectal cancer is neoadjuvant chemoradiotherapy (CRT) followed by surgery. Neoadjuvant CRT has been shown to decrease physical fitness, and this decrease is associated with increased post-operative morbidity. Exercise training can stimulate skeletal muscle adaptations such as increased mitochondrial content and improved oxygen uptake capacity, both of which are contributors to physical fitness. The aims of the EMPOWER trial are to assess the effects of neoadjuvant CRT and an in-hospital exercise training programme on physical fitness, health-related quality of life (HRQoL), and physical activity levels, as well as post-operative morbidity and cancer staging.

**Methods/Design:**

The EMPOWER Trial is a randomised controlled trial with a planned recruitment of 46 patients with locally advanced rectal cancer and who are undergoing neoadjuvant CRT and surgery. Following completion of the neoadjuvant CRT (week 0) prior to surgery, patients are randomised to an in-hospital exercise training programme (aerobic interval training for 6 to 9 weeks) or a usual care control group (usual care and no formal exercise training). The primary endpoint is oxygen uptake at lactate threshold ($$ \overset{\cdotp }{\mathrm{V}}{\mathrm{o}}_2 $$ at $$ {\widehat{\uptheta}}_{\mathrm{L}} $$) measured using cardiopulmonary exercise testing assessed over several time points throughout the study. Secondary endpoints include HRQoL, assessed using semi-structured interviews and questionnaires, and physical activity levels assessed using activity monitors. Exploratory endpoints include post-operative morbidity, assessed using the Post-Operative Morbidity Survey (POMS), and cancer staging, assessed by using magnetic resonance tumour regression grading.

**Discussion:**

The EMPOWER trial is the first randomised controlled trial comparing an in-hospital exercise training group with a usual care control group in patients with locally advanced rectal cancer. This trial will allow us to determine whether exercise training following neoadjuvant CRT can improve physical fitness and activity levels, as well as other important clinical outcome measures such as HRQoL and post-operative morbidity. These results will aid the design of a large, multi-centre trial to determine whether an increase in physical fitness improves clinically relevant post-operative outcomes.

**Trial registration:**

ClinicalTrials.gov NCT01914068 (received: 7 June 2013). Sponsor: University Hospital Southampton NHS Foundation Trust.

## Background

The standard treatment pathway for magnetic resonance (MR)-defined, locally advanced rectal cancer is neoadjuvant chemoradiotherapy (CRT) followed by total mesorectal excision surgery [1, 2]. Chemotherapy, combined with radiotherapy, improves local disease control and local recurrence for locally advanced rectal cancer [3–5]. With optimised local treatment, including neoadjuvant CRT and surgery, local relapse rates have now been reduced to less than 10 % [2]. Cancer is associated with cachexia, which, in the pre-operative period, has been shown to influence perioperative outcome, increasing the risk of complications, mortality and length of hospital stay in major gastrointestinal surgery [6]. Chemotherapy has been related to skeletal muscle wasting, oxidative stress, mitochondrial death [7] and reduced *in vivo* mitochondrial function [8]. Furthermore, cancer treatment has been linked to decreased physical fitness levels, which appear to be related to the type of treatment; that is, physical fitness is lower in those receiving surgery and radiotherapy in combination with chemotherapy than in those who receive radiotherapy or surgery alone [9]. Neoadjuvant CRT has been shown to be associated with a decrease in objectively measured physical fitness, as measured by cardiopulmonary exercise testing (CPET) in those with locally advanced rectal cancer [10]. This decrease in physical fitness was in turn shown to be associated with increased short-term post-operative morbidity [10]. Moreover, a decrease in physical fitness has also been shown in a group of upper gastrointestinal cancer patients following neoadjuvant chemotherapy [11]. In this case, the change was associated with 1-year mortality [11].

CPET is a good pre-operative risk assessment tool as it provides an objective global assessment of the integrative responses of the pulmonary, cardiovascular and musculoskeletal systems rather than evaluating the function of individual organ systems in isolation [12]. Furthermore, as a dynamic assessment, CPET provides more insight than a resting test into the response to physiological stress. The perioperative period is a time of physiological stress as the surgical stress response increases the metabolic rate, and consequently, tissue oxygen demand rises. By detecting abnormal exercise capacity and, consequently, reduced physiological reserve, CPET identifies patients at increased risk of complications and mortality. CPET is increasingly being used preoperatively to identify patients at high risk of perioperative morbidity and mortality [13–15].

Exercise training can stimulate skeletal muscle adaptations such as increased mitochondrial content and improved oxygen uptake capacity [16], both of which are contributors to physical fitness and could possibly reduce the adverse effects of cancer treatment. In 2013, Jones and Aflano [17] reported a series of observational studies that suggest higher levels of exercise may be associated with an improved prognosis in patients with solid tumours. Physical fitness is a modifiable prognosticator, and women with breast cancer who exercise at moderate intensity, 30 minutes or more per day on 5 days or more per week have been reported to have a lower risk of death [18]. Furthermore, women who were physically active following diagnosis of non-metastatic colorectal cancer have been shown to have a significantly lower risk of colorectal cancer–specific death or death from any cause [19]. Our group (Fit-4-Surgery) has previously shown in a non-randomised study that a 6-week moderate to severe intensity, interval exercise training programme, following neoadjuvant CRT and prior to surgery in patients with locally advanced rectal cancer resulted in a clinically relevant increase in physical fitness [20] and HRQoL [21].

In this manuscript, we describe the design of a parallel group randomised controlled multi-centre trial comparing an in-hospital exercise training programme to a usual care control group in patients undergoing neoadjuvant CRT and elective surgery for locally advanced rectal cancer. To the best of our knowledge, the EMPOWER trial is the first RCT of such an intervention in a neoadjuvant setting.

### Aims

The aims of this study are to evaluate the following hypotheses:

### Primary hypothesis

A 9-week, in-hospital, exercise training programme compared with a usual care control group (usual care; no formal exercise training) will result in a clinically significant difference in oxygen uptake at lactate threshold ($$ \overset{\cdotp }{\mathrm{V}}{\mathrm{o}}_2 $$ at $$ {\widehat{\uptheta}}_{\mathrm{L}} $$; 2.0 mL.kg^-1.^min^−1^) assessed using CPET, following neoadjuvant CRT prior to elective cancer surgery.

### Secondary hypothesis

An in-hospital exercise training programme compared with a usual care control group (usual care; no formal exercise training) will result in an improvement in psychological health benefits as assessed using semi-structured interviews and questionnaires such as the EORTC QLQ-30 and EQ-5D following neoadjuvant CRT prior to cancer surgery.Neoadjuvant CRT will result in a reduction in $$ \overset{\cdotp }{\mathrm{V}}{\mathrm{o}}_2 $$ at $$ {\widehat{\uptheta}}_{\mathrm{L}} $$ as assessed using CPET.

### Exploratory hypotheses

A 9-week in-hospital exercise training programme compared with a usual care control group (usual care; no formal exercise training) will be associated with 1) greater physical activity, assessed using SenseWear accelerometer, following neoadjuvant CRT prior to cancer surgery; 2) lower day 5 surgical morbidity (using POMS); and 3) improved Magnetic Resonance (MR)-defined local rectal cancer staging assessed using the TNM classification system (tumour, nodes, metastasis) and tumour regression grading (mrTRG).

## Methods/Design

### Study design

The EMPOWER Trial is a parallel group randomised controlled trial in locally advanced rectal cancer patients undergoing both neoadjuvant CRT and elective surgery. The trial is funded by the National Institute for Health Research - Research for Patient Benefit Programme (PB-PG-0711-25093), approved by North West Centre for Research Ethics Committees (13/NW/0259) and registered with clinicaltrials.gov (NCT01914068).

### Participants

Eligibility criteria for inclusion at cancer diagnosis include the following: age ≥ 18 years, with MR-defined, locally advanced (circumferential resection margin threatened), resectable rectal cancer (≥ T2N + M0), undergoing standardised neoadjuvant CRT; with no distant radiological defined metastasis. Exclusion criteria include the following: inability to give informed consent, non-resectable disease, distant metastasis, inability to perform CPET or bicycle exercise, and patients who declined surgery or neoadjuvant CRT or who received non-standard neoadjuvant CRT. Figure 1 provides an algorithm of the clinical pathway and the complete series of assessments for the duration of the trial.

**Fig. 1 Fig1:**
[figure not shown]
The EMPOWER trial algorithm presented illustrates the patient pathway and the time points of assessments and intervention as part of the trial

### Recruitment and randomisation

The EMPOWER trial is currently recruiting (start date is August 2013; end date is December 2015). All potentially eligible patients are being identified at multi-disciplinary meetings and approached with written information about the trial at the oncology/surgical outpatient appointment. Patients are contacted by telephone to provide additional information about the trial and to confirm their eligibility. If the patient chooses to participate in this trial, the first research visit is organised where written informed consent is obtained and all baseline measurements are undertaken. Following neoadjuvant CRT (week 0), patients are allocated to the in-hospital exercise training group or usual care control group. Patients are randomised (1:1) to either an in-hospital exercise training programme or usual care control group using the Trans European Network for patient randomisation in clinical trials system (TENAELA System).

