#### Exercise training frequency

Patients are requested to attend three in-hospital exercise training sessions per week for 6 to 9 weeks (dependent on the time interval between neoadjuvant CRT and surgery at each hospital).

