### Outcome measurements

All patients undergo a series of outcome measure assessments throughout the period of the trial: baseline (pre-neoadjuvant CRT), mid-neoadjuvant CRT and at several time points following completion of the neoadjuvant CRT (weeks 0, 3, 6 and 9) prior to surgery (surgery generally takes place between weeks 6 and 9, depending on the hospital). In UHS only, based on the clinical pathway, some patients are treated with neoadjuvant chemotherapy (four cycles) followed by neoadjuvant CRT. In this instance, an additional research visit is scheduled halfway between the completion of chemotherapy and commencing CRT). The outcome measures used in the EMPOWER trial are summarised in Table 1.

**Table 1 Tab1:** Outcomes and assessment measures used in the EMPOWER trial

Outcomes	Assessment measure	Pre CRT	Mid chemo-CRT	Mid CRT	Week 0	Week 3	Week 6	Week 9	Day 3 post-surgery	Day 5 post-surgery	Day 8 post-surgery	Day 15 post-surgery	6 Weeks post-surgery
Primary endpoint													
Oxygen uptake at lactate threshold	CPET	X	UHS only		X	X	X	X					
Secondary endpoint													
Health-related quality of life	Questionnaires: EORTC QLQ-30, EQ-5D	X	UHS only	X	X	X	X	X					X
	Semi-structured interviews				X			X					
Physical activity	SenseWear accelerometer	X	UHS only	X	X	X	X	X					
Exploratory endpoint													
Post-operative morbidity	POMS								X	X	X	X	
Cancer staging	MR pelvis mrTRG	X						X					
								X					

*Abbreviations*: *CRT* chemoradiotherapy, *CPET* cardiopulmonary exercise test, *UHS* University Hospital Southampton, *POMS* Post- operative morbidity score, *mrTRG* magnetic resonance tumour regression grade, *MR* magnetic resonance

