### Primary outcome

#### Physical fitness

CPET is used to assess physical fitness over a series of time points (which vary in each hospital depending on the cancer treatment and time interval between CRT and surgery): baseline (pre-neoadjuvant CRT); mid chemotherapy-CRT (in UHS only); and post-neoadjuvant CRT (week 0), week 3, week 6 and week 9. All CPETs are performed in the hospital by trained and experienced staff. Every effort is made to coordinate research visits with other clinical appointments. Each CPET is conducted at a similar time of day. Participants are asked to refrain from caffeine and strenuous exercise prior to the test. All CPETs are performed using an electromagnetically-braked cycle ergometer (Ergoline 2000), a 12-lead ECG, non-invasive blood pressure measurement and pulse oximetry, and a metabolic cart (Geratherm Respiratory GmbH, Love Medical Ltd). The incremental rise in work rate is pre-determined using the equation derived by Wasserman and colleagues [22] in which the same work-rate protocol is used for each CPET. This is done in an objective manner aiming for a test duration between 8 and 12 minutes. The ramp protocol equation is as follows:$$ \begin{array}{c}\hfill \overset{\cdotp }{\mathrm{V}}{\mathrm{o}}_2\kern0.24em \mathrm{unloaded}\kern0.24em \left(\mathrm{ml}.mi{n}^{-1}\right)=150+\left(6\times \mathrm{weight}\kern0.24em \left(\mathrm{kg}\right)\kern0.24em \right)\hfill \\ {}\hfill \overset{\cdotp }{\mathrm{V}}{\mathrm{o}}_2\kern0.24em \mathrm{at}\kern0.24em \mathrm{Peak}\kern0.24em \left(\mathrm{ml}.mi{n}^{-1}\right)\kern0.24em \mathrm{Men}=\left[\mathrm{height}\kern0.24em \left(\mathrm{cm}\right)-\mathrm{age}\left(\mathrm{y}\right)\right]\times 20\hfill \\ {}\hfill \overset{\cdotp }{\mathrm{V}}{\mathrm{o}}_2\; at\kern0.24em \mathrm{Peak}\left(\mathrm{ml}.mi{n}^{-1}\right)\kern0.24em \mathrm{Women}=\left[\mathrm{height}\kern0.24em \left(\mathrm{cm}\right)-\mathrm{age}\left(\mathrm{y}\right)\right]\times 14\hfill \\ {}\hfill \mathrm{Work}\kern0.24em \mathrm{Rate}\kern0.24em \mathrm{increment}\kern0.24em \left(\mathrm{W}.mi{n}^{-1}\right)=\mathrm{Peak}\kern0.24em \overset{\cdotp }{\mathrm{V}}{\mathrm{o}}_2-\left.\overset{\cdotp }{\mathrm{V}}{\mathrm{o}}_2\kern0.24em \mathrm{Unloaded}\right)/100\hfill \end{array} $$

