### Data analysis

#### Sample size calculation

A sample of 46 patients is required to detect a difference between groups of 2.0 mL.kg^-1.^min^−1^$$ \overset{\cdotp }{\mathrm{V}}{\mathrm{o}}_2 $$ at $$ {\widehat{\uptheta}}_{\mathrm{L}} $$ using a two-sample t-test at the 5 % significance level with 90 % power. This is based on a standard deviation of the change in $$ \overset{\cdotp }{\mathrm{V}}{\mathrm{o}}_2 $$ at $$ {\widehat{\uptheta}}_{\mathrm{L}} $$ values of 1.8 ml.kg^−1·^min^−1^ and is inflated to allow for 20 % patient drop-out [29]. This estimate was calculated using the sampsi function in Stata/IC 12.0.

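### Hospital sets the CRT-to-surgery interval, yet the main t-test has no term for it: adding a two-level interval factor is a cheap improvement

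*Protocol article*

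**What the plan says.** **Hospital as a structural variable.** Under Exercise training frequency, the programme lasts 6 to 9 weeks, "dependent on the time interval between neoadjuvant CRT and surgery at each hospital". Under Outcome measurements, surgery falls between weeks 6 and 9 according to hospital. Under Physical fitness, the CPET time points are ones "which vary in each hospital depending on the cancer treatment and time interval between CRT and surgery". One hospital has a further pathway: "In UHS only, based on the clinical pathway, some patients are treated with neoadjuvant chemotherapy (four cycles) followed by neoadjuvant CRT". The SPIRIT table lists five hospitals and allows more to be opened.

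**Allocation.** Recruitment and randomisation states: "Patients are randomised (1:1) to either an in-hospital exercise training programme or usual care control group using the Trans European Network" system. The sequence-generation row of the SPIRIT table repeats this. Neither place mentions stratification, minimisation or blocking, and neither says that allocation is unstratified.

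**Analysis.** The sample size is for a comparison "using a two-sample t-test at the 5 % significance level with 90 % power". Statistical analyses names the same test, with a 95 % confidence interval, for the effect on physical fitness. A linear regression with up to three covariates, not named, is added to test sensitivity to covariates. A linear mixed model then compares fitness at each time-point. Hospital is mentioned in neither.

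**The concern.** The article identifies a factor, known before randomisation, that governs how long patients are followed before surgery, how long the exercise arm trains and which CPETs are held. It is reasonable to expect this factor to be related to the change in oxygen uptake at lactate threshold. A comparison of two arm means has no place for it.

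Two things follow. If allocation is not balanced on hospital type, the arms may by chance contain different mixes, and the unadjusted difference carries that imbalance in full. If allocation is balanced on it, the t-test leaves the between-type variation in its error term and overstates the standard error. The trial is also meant to supply an effect size for a definitive trial (Discussion), so a chance shift would carry forward.

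**Working it through.** **1. The plan's own figure.** "A sample of 46 patients is required to detect a difference between groups of 2.0" mL/kg/min, with SD of change 1.8, two-sided 5 % (two-sided assumed) and 90 % power.
- n per arm = 2 × [1.8 × (1.960 + 1.282) / 2.0]² = 17.02, rounded up to 18.
- The text adds "and is inflated to allow for 20 % patient drop-out": 18 / 0.8 = 22.5, so 23 per arm and 46 in total. The stated figure reproduces.
- Standard error with 18 per arm analysed: 1.8 × √(2/18) = 0.60. Power of the t-test is 89.9 %.

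**2. Chance imbalance.** Assumption: 23 of the 46 patients are at long-interval hospitals and the arms are 23/23 without stratification. The number of long-interval patients in one arm is hypergeometric (46, 23, 23).
- SD of the difference in shares: 0.149, i.e. 15 percentage points.
- P(difference of 20 points or more) = 0.24. P(30 points or more) = 0.076.
- With a long-interval share of 30 % instead of 50 %, the SD is 14 points.

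**3. Effect on the estimate.** Unadjusted difference = true effect + (imbalance × gap), where the gap is the difference in mean change between hospital types. The documents give no gap, so a range is assumed.

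| Assumed gap (mL/kg/min) | Shift at 15 points (1 SD) | Shift at 30 points | 30-point shift as share of 2.0 |
|---|---|---|---|
| 0.5 | 0.075 | 0.15 | 7.5 % |
| 1.0 | 0.15 | 0.30 | 15 % |
| 2.0 | 0.30 | 0.60 | 30 % |

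**4. Error rates with 36 analysed, half in each type, total SD held at 1.8.** The within-type variance is w = 3.24 − gap²/4.
- *Unstratified allocation, t-test:* simulated type I error stays near 5 % and power near 90 % at every gap.
- *Unstratified allocation, two-level term added:* given imbalance d, the variance of the estimate is w × (2/18) / (1 − d²). Averaging the power over d gives 89.0 % (gap 0), 89.5 % (0.5), 91.2 % (1.0) and 96.9 % (2.0). Against 89.9 % for the t-test, that is just under one point lost at gap 0, about one gained at 1.0 and about seven gained at 2.0.
- *Stratified allocation, t-test:* the pooled variance is about w + 36 × (gap²/4) / 34. At gap 1.0 it is 2.99 + 0.265 = 3.255. The effective critical value is then 2.032 / √(2.99/3.255) = 2.12, so type I error is about 4 %. At gap 2.0 it is 2.24 + 1.059 = 3.299, with critical value 2.032 / √(2.24/3.299) = 2.47 and type I error about 2 %. At gap 0.5 the error is 4.8 %, close to nominal.

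**5. Why not one term per hospital.** A simulation used five hospitals of 14, 9, 6, 4 and 3 analysed patients (assumed) without stratification. Adjusting for all five gave about 85 % power with no between-hospital variation and 89 % at an intra-hospital correlation of 0.1, against about 90 % for the t-test in both cases.

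**The case against.** The strongest reply has five parts.

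- **Silence on stratification is not evidence of simple randomisation.** A journal article commonly leaves such factors to the full protocol. This stands. A reader might infer that allocation ignores hospital, but the article does not say so.
- **Hospital may yet enter the analysis.** The sensitivity regression could include hospital or interval group among its unnamed covariates. This also stands, but the main test is fixed here as a t-test, which cannot.
- **Chance imbalance is not bias.** A reader might infer that exercise would be credited with natural recovery. Over repeated randomisations the estimate is unbiased, and the confidence interval already allows for such imbalance. The documents also describe no recovery in usual-care patients, and no effect of prior chemotherapy on recovery.
- **The interval mechanism depends on the assessment compared.** At the week 6 CPET, patients who attend are at the same time since CRT whatever their hospital. The gap may then be small. It would matter more if the last CPET before surgery is used.
- **The pathway difference is partial.** Only some patients at one hospital have chemotherapy first, so a hospital or interval term would not cleanly capture it.

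What survives is that the stated main test makes no use of a factor that the article itself treats as structural. That costs interpretability or precision whether or not allocation is stratified.

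**Conclusion.** The point holds as a modest improvement to the method. It is not a flaw that invalidates the trial, and the documents do not support reading it as systematic bias or as proof that randomisation is unstratified.

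If hospital types differ by 1.0 mL/kg/min, an imbalance seen in about 8 % of trials moves the estimate by 0.3, half a standard error. At a gap of 0.5 the same imbalance moves it by a quarter of a standard error, and at 2.0 by a full one. If allocation is in fact stratified, the t-test's true level is about 4 % at a gap of 1.0 and about 2 % at 2.0.

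These sizes rest on an assumed half share of patients at long-interval hospitals and on assumed gaps. The documents give no recruitment by hospital and no between-hospital variation. If hospital types do not differ, nothing is lost under the current plan.

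**What to change.** 1. Replace the main two-sample t-test with a linear model containing arm and a two-level term for short versus long CRT-to-surgery interval hospital, or the stratification factor actually used. Report the adjusted difference with its 95 % confidence interval. Do not use five hospital indicators.
2. Classify each hospital by its usual interval, fixed before any comparison of arms and on opening for new hospitals. Do not use each patient's actual interval, which arises after randomisation.
3. State whether allocation is balanced on hospital or interval. If it is not, add the two-level factor as a stratification or minimisation factor for remaining allocations. Patients already randomised are covered by the model term.

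Cost: one degree of freedom, a setting in the existing randomisation system, and just under one point of power (89.9 % to 89.0 %) if hospital types do not differ and allocation stays unstratified. Short blocks within strata would make allocation somewhat more predictable. Varying block sizes, or minimisation with a random element, limits this.
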